**Fig. 2 Fig2:**
[figure not shown]
Maps of the study site. **a** The Philippines; **b** Lipa City *barangay*s

### Outcomes

The principle evaluation criterion is the epidemiological efficacy read out: dengue infection sero-conversion. Sero-conversion to dengue virus exposure will be measured by an enzyme-linked immunosorbent assay (ELISA) for immunoglobulin (Ig)G titres using repeated saliva samples taken sequentially during three cross-sectional studies at months 0, 3 (end of month 2), and 5 (end of month 4) during the intervention (In2Care® trap placement) period each year in both treatment and control sites. These time points are designated Pre-, Post1, and Post2 within each year.

The secondary evaluation criterion is the entomological read out. To measure the impact of the In2Care® traps on the adult mosquito population densities, 20 GATs will be placed in each of 10 randomly selected treatment and 10 control sites matched with intervention sites for historical dengue incidence. *Aedes* spp. (both *Ae. aegypti* and *Ae. albopictus*) adults will be counted and identified in the GATs once each week beginning 2 weeks before intervention, throughout the intervention period, and 2 weeks post-intervention. Traps will be placed both inside and outside 10 randomly selected houses within each site. Traps placed outside will be positioned against the wall of the house in an area with shelter from direct sunlight. Traps placed inside the house will be positioned in a suitably unobstructed area but where there is air movement.

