Recently, a commercialised AD device, the In2Care® mosquito trap (In2Care® BV, Wageningen, Netherlands) [26], has been validated in field studies in the Grand Cayman, yielding pupal mortality rates of ~ 60% (unpublished data). The In2Care® trap attracts ovipositing *Ae. aegypti* females, which are then contaminated with a combination of PPF and an entomopathogenic fungus, *Beauvaria bassiana*, a United States Environmental Protection Agency approved agent that has been used in biological control of many agricultural pests for decades [27]. The lethal and pre-lethal (e.g. reduced feeding propensity) effects of the fungus have been described in *Anopheles* and *Aedes* species in which it takes several days to kill the adult insect, thereby allowing the mosquito to disseminate the PPF component [28, 29]. The fungal infection also interferes with DENV replication within the mosquito, thus having a profound effect on mosquito vectorial capacity (i.e. transmission efficacy) beyond that of shortening the adult mosquito lifespan [30]. The In2Care® mosquito trap thus uses an AD approach to disseminate a pupacide combined with a direct action, slow-acting entomopathogenic adulticide.

This study proposes to evaluate the epidemiological and entomological efficacy of the In2Care® trap in a dengue-endemic urban location in the Philippines.

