**Fig. 1 Fig1:**
[figure not shown]
Intervention and sampling strategy. The yellow region includes recruited children for the sero-conversion study and the outer peripheral region is the buffer zone also treated with AD devices (blue jar icons) but without sero-conversion saliva sampling

Adult *Aedes* mosquito densities will be monitored in treatment and control sites by the use of Gravid *Aedes* Traps (GATs; Biogents AG, Regensburg, Germany) (Additional file 1). GATs are more efficient in capturing gravid *Ae. aegypti* than sticky ovitraps and are practical, low cost, and easily transportable devices, essential attributes in large-scale monitoring programmes [33].

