In2Care® traps will be placed in open areas outside of the house. GATs will be placed inside and outside houses at designated locations. GATs will be assembled as per the manufacturer’s instructions and filled with water to which a handful of dry grass/hay will be added. A sticky strip is placed inside the GAT and used to capture entering mosquitoes (Additional file 3). The general state of the traps (In2Care® and GATs) will be assessed during the weekly GAT counts and water replenished where necessary. Likewise, the dried grass and water in the GATs will be replaced during the weekly survey. After 6 weeks, the netting, active ingredient, and yeast tablets from the sachet of the In2Care® mosquito trap will be replaced with a new sachet and new water. At the end of the 4-month treatment period, all mosquito traps will be removed, properly cleaned, and stored until the following year.

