This efficacy trial of the first commercial product using the AD approach will be highly informative as to the general utility of AD in reducing not only vector mosquito densities but, more importantly, actually reducing the risk of dengue infection. The AD technique may complement typical source reduction practices and larviciding campaigns by more efficiently targeting the most productive containers upon which the female mosquito fixes and contaminates the larval habitat, and importantly those sites beyond access for human manual treatment. AD is potentially a more effective intervention than adult mosquito lethal traps because its impact is amplified between the dissemination devices and the larval habitats, in other words a small number of devices can contaminate a much wider number of habitats [12, 16]. Despite some evidence that PPF disseminated by AD can be effective [12, 15, 23], there remain several obstacles to be overcome. Firstly, the AD devices need to attract sufficient mosquitoes and thus depend not only on the local abundance of mosquitoes but also on the attractiveness of the AD device in the face of other competitive sites. Secondly, studies in urban areas have shown that topography is important for the movement of mosquitoes (e.g. solid structure barriers impeding dissemination) [45]. This implies that AD devices may have to be deployed at very high and operationally impracticable densities. Furthermore, the In2Care® recommendation in areas having high numbers of potential alternative larval habitats is 1 device every 400 m^2^, the equivalent to one trap per 20 m. This high trap density is unlikely to be feasible or even welcome by a community. Thus, there is need for the development of more operationally useful and practical strategies for incorporation of AD approaches into larger, integrated mosquito control programmes. Finally, as with all insecticides, the risk of resistance developing against PPF is a real possibility; therefore, resistance management strategies are required to mitigate this threat.

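### The in-season arm difference in GAT catch may partly be diversion of egg-laying females to In2Care traps, and the trap-removal text puts in doubt the weeks that could help tell this from lower density

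*Protocol article*

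**What the plan says.** **What each device attracts.** The Background of the protocol article states: "The In2Care® trap attracts ovipositing *Ae. aegypti* females". The Intervention section adds yeast tablets whose odour is meant to draw egg-laying mosquitoes. Of the monitoring trap, the Study type section says: "GATs are more efficient in capturing gravid *Ae. aegypti* than sticky ovitraps". The Intervention section baits the GAT with water and dry grass or hay.

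**Where they stand.** In2Care traps are placed in the 23 treated clusters only, outdoors, at one per 1000 m². GATs stand in 10 treated and 10 control sites, inside and outside 10 houses per site.

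**How density is read.** Outcomes describes no other adult-density measure: "To measure the impact of the In2Care® traps on the adult mosquito population densities, 20 GATs will be placed". The statistical section models mosquitoes per trap per week, with week and intervention as fixed effects. A second analysis uses the distance from each GAT to the nearest In2Care trap.

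**When GATs are counted.** Outcomes plans weekly counts from two weeks before, "throughout the intervention period, and 2 weeks post-intervention". The Intervention section says: "At the end of the 4-month treatment period, all mosquito traps will be removed, properly cleaned, and stored until the following year". A few sentences earlier, that section uses the word traps explicitly for both devices.

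**Rank of the outcome.** The Objectives section names adult density in the primary objective. Outcomes calls the entomological readout secondary.

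**The concern.** The treatment can act on the measuring instrument as well as on the mosquito population. Adding many attractive egg-laying sites to one arm gives each female more places to go, so fewer may reach a GAT even if the number of females is unchanged. The in-season arm contrast then mixes suppression with diversion, and diversion pushes it in the product's favour. The pre-intervention weeks cannot correct this, because diversion starts when the traps arrive.

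The distance analysis does not resolve it. Suppression and diversion both predict a lower catch close to an In2Care trap.

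Within a season, the only counts after baseline with no In2Care trap present are the two post-intervention weeks, and the removal sentence, read literally, deletes them. At stake is whether a lower catch can be reported as lower density.

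**Working it through.** **1. Trap numbers (Intervention and Outcomes sections).**
- Treated area with a 140 m sampling radius and a 50 m buffer: π × 190² = 113,411 m². At one trap per 1000 m² this gives 113 devices, which reproduces the protocol's figure.
- GATs per monitored site: 10 houses × 2 positions = 20, which also reproduces.
- In2Care traps per GAT in a treated, monitored cluster: 113 / 20 = 5.65. In a control cluster: 0.

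**2. Possible size of diversion at unchanged density (illustration).** Suppose a female chooses sites in proportion to their number and attractiveness. Let N be the natural containers per cluster, each as attractive as a GAT, and let a be the attractiveness of an In2Care trap relative to a GAT. The documents give neither, so both are assumptions. The treated-to-control catch ratio with no true effect is

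(20 + N) / (20 + N + 113a).

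For example, with N = 500 and a = 1 it is 520 / 633 = 0.821, a fall of 17.9%.

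| N | fall, a = 1 | fall, a = 0.5 | fall, a = 0.25 |
|---|---|---|---|
| 100 | 48.5% | 32.0% | 19.1% |
| 250 | 29.5% | 17.3% | 9.5% |
| 500 | 17.9% | 9.8% | 5.2% |
| 1000 | 10.0% | 5.2% | 2.7% |
| 5000 | 2.2% | 1.1% | 0.6% |

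**3. Allowing for repeat visits.** In2Care traps do not hold females. If each female makes five site visits, the chance of reaching a GAT is 1 − (1 − 20/T)^5, with T = 20 + N + 113a in treated clusters and T = 20 + N in control clusters. At a = 1 the fall becomes 16.7% instead of 17.9% for N = 500, and 39.6% instead of 48.5% for N = 100. Five visits is also an assumption.

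**4. Could such a fall be declared significant?** Take the 17.9% case (0.197 on the log scale), 10 versus 10 clusters, a two-sided 5% test and the normal approximation. The between-cluster SD of log catch is assumed. The probability of a significant result with no change in density is 0.99, 0.59, 0.31 or 0.14 for an SD of 0.1, 0.2, 0.3 or 0.5. For N = 5000 and a = 0.25 it is about 0.03 at every one of these SDs, which is no more than chance in that direction.

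**5. Counting rounds.** Four months is 4 × 52 / 12 = 17.3 weeks. With two weeks before and two after, there are about 21.3 weekly rounds a year. In all of the roughly 17 intervention weeks the In2Care traps stand beside the GATs. Post-baseline rounds without them number 2 under Outcomes and 0 if the removal sentence covers the GATs.

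**The case against.** - **The size is unknown and may be trivial.** The Background says that treating every breeding site by hand is unrealistic, which points to many natural containers, and with many containers diversion shrinks to a few percent or less. This stands. A reader might infer that GAT catch must fall by a definite amount such as 10 to 30%. The documents do not support that, because any such figure comes from assumed container numbers and attractiveness.
- **Females are not retained.** Skip-oviposition and a fungus that takes days to kill mean that a female who visits an In2Care trap can still reach a GAT. This stands, but under the repeat-visit model it reduces diversion only modestly.
- **Indoor GATs.** Half the GAT positions are indoors and the In2Care traps are outdoors, so the devices do not mix freely. This stands, and it offers a free contrast.
- **The competition remark.** The Discussion's phrase "the attractiveness of the AD device in the face of other competitive sites" concerns In2Care traps against natural habitats and does not mention GATs. This is correct, and it supports the point only by showing that egg-laying sites compete.
- **The removal sentence is general clean-up text.** Outcomes is more specific, and the schedule in Fig. 3 is not shown and may settle the timing. A reader might infer that the post-intervention counts will be lost. The text shows only that two sections conflict.
- **Two post weeks are a poor sole test.** They are about 2 of 21 rounds in 10 versus 10 sites. Adult exposure to the fungus stops on removal, and mosquitoes can enter from outside the cluster, so a real in-season reduction could be missed. This stands. It rules out requiring the post-week contrast to succeed before density is claimed.

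**Conclusion.** The point holds with limits. The two devices target females at the same stage, and In2Care traps stand in one arm only, so the in-season difference in GAT catch may include diversion that favours the product. Only the direction follows from the documents. The size runs from about 49% to under 1% across the assumptions tried, and none of these values can be preferred from the text. Neither the arm contrast nor the distance analysis can separate diversion from suppression.

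The conflict between Outcomes and Intervention over GATs after month four is in the text itself and needs resolving whatever the size of the bias. The two pre-intervention weeks are also free of In2Care traps, but they cannot show that season's effect.

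A reader might infer that the trial's main result is compromised. It is not. Sero-conversion is the principal criterion and does not depend on GATs, and the sample size is untouched. The point limits what a lower GAT catch can support. That still matters, because the Objectives section names adult density.

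**What to change.** 1. Reconcile the Intervention section with Outcomes so that the GATs stay for the two planned post-intervention weeks after the In2Care traps are taken away.
2. Keep the in-season GLMM as the main entomological analysis, but report its result as GAT catch, an oviposition-trap index. State that a lower in-season catch alone does not establish lower density.
3. Pre-specify two supportive analyses: the arm contrast in the post weeks, adjusted for the two pre-intervention weeks, and the arm effect separately for indoor and outdoor GATs. A difference that vanishes as soon as the In2Care traps leave, or that appears only outdoors, would point towards diversion.
4. Treat the distance analysis as descriptive.

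**Cost.** Wording and two extra model fits. The GAT weeks are already planned. The post-week contrast will be imprecise and may understate a real effect as suppression wanes or mosquitoes immigrate, and females moving between indoors and outdoors will blur the second contrast. Both should inform interpretation and not gate the claim.

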### Study type

The study is a parallel, two-armed cluster randomised trial (PCRT) evaluating the efficacy of the In2Care® mosquito trap for reducing incidence of dengue infection over a 2-year period using 4 consecutive months of treatment each year.

Previous studies have estimated that, to account for the unpredictable spatio-temporal heterogeneity in dengue transmission, PCRTs are the most effective study design and that a larger number of clusters with fewer children per cluster provide the optimal strategy—in effect, a bet-hedging approach for a statistically sufficient coverage of an area [31]. In order to attempt to control for the spatial heterogeneity in dengue occurrence, 46 areas (hereafter referred to as “clusters”), each of approximately 200 m in radius, will be pre-selected. Twenty-three clusters will be assigned to the treatment arm with In2Care® traps and 23 to the control arm without traps. Cluster sites assigned to treatment versus control arms will be matched according to retrospective incidence of reported dengue clinical cases over the previous 5 years and human population density (See Stratification scheme below). Because of ‘edge effects’, where individuals near the periphery of the treatment area will be potentially subject to contact with mosquitoes coming from neighbouring non-treated areas, we will implement the “fried egg” design [32] whereby we will assess sero-conversion only in children resident at least 50 m from the treatment zone edge. Thus, whilst we will implement In2Care® traps throughout a 200 m radius circle, we will only consider sero-conversion in children within a 150 m radius (Fig. 1). One hundred schoolchildren (between 6 and 16 years of age) will be recruited for repeated sero-conversion observation within the inner circle of each of the 46 clusters (See Sample size calculations below). As the population density in clusters will vary, it is possible that there will not be sufficient children within a prescribed area. In this case, we will increase the circle radius to reach the required sample number.

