### Stratification scheme

Clusters will be stratified according to historical dengue incidence and population density. In the Philippines, a *barangay* is the smallest administrative division in the Philippines (urban or rural), but which can be subdivided into *puroks* (zones) consisting of 20 to 50 households depending on the location and density of the households in an area. The previous 5 years of dengue incidence data at the *purok* administrative unit level will be acquired from the Philippines Integrated Disease Surveillance and Response (PIDSR) system to identify relative defined ‘hotspots’ and ‘coldspots’ of dengue activity during that period. This information will be entered into the Disease Data Management System (DDMS+) (see Data management below) along with information on geography, population density, and infrastructure at the *barangay* level. This will generate maps with which to choose clusters for the intervention study and assign clusters to either treatment or control groups according to broad similarities.

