### Recruitment

In each *barangay* pre-selected to participate in the study, Research Institute for Tropical Medicine (RITM) team members will hold general information meetings on the project with the population in the presence of the community (*barangay*) health workers (BHWs) and local public health officials. Because the volunteers to be recruited are of school age, additional information meetings will be held in the local schools. Once clusters are identified and randomly assigned with appropriate stratification, the study team will perform household visits with the Lipa City public health staff and respective area BHWs. The visit will explain the study and study protocol in detail and request individual informed consent/assent for periodic saliva sampling and mosquito trap placement by each household head (In2Care® and/or GATs) in and around participant’s houses (See Ethics approval and consent to participate below).

Following signed consent, a short questionnaire pertaining to the participant will be completed and the individual assigned a unique identifier barcode. The questionnaire will be completed on paper including details on: name, address, age, sex, whether having received the Dengvaxia® vaccine (and if yes, how many injections) or not, and the attending school and year (grade). The individual’s barcode will be placed next to their name on the consent form and kept in a separate file. Subsequent samples will also be labelled with a unique barcode and linked back to the individual’s barcode in the questionnaire.

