#### Adult mosquito spatial distributions (relative densities) using GATs

Weekly adult mosquito catches will be analysed by fitting a GLMM with the response variable as mosquitoes/trap/week, time (week), and intervention (Y/N) as fixed effects, and cluster ID and cluster risk designation as random effects. In addition, we will include occurrence of any public health mosquito control intervention performed in the cluster by counting the numbers of days during the 2 month inter-saliva sampling period when mosquito numbers could have been affected by such a control intervention (up to 14 days maximum post-control) as a random factor. We will test for over-dispersion in the response variable and, if it exists, an over-dispersion parameter will be estimated and applied. Otherwise, a Poisson distribution will be assumed. Two models will be constructed, one for each *Aedes* dengue vector species.

Additionally, a second series of analyses involving the distance of GATs from the nearest In2Care® trap will be analysed using log-linear regression, fitting the actual Euclidean distance in metres as a continuous variable. Because the extent to which an area is built up can impede mosquito flight (i.e. barriers), each cluster will be categorised into an urban typology (categorical building density) and this will be fitted as a factor in the analyses.

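### The mosquito-trap comparison names historical incidence as its only matching factor for control clusters, does not tie them to the counterparts already matched on population density, and has no density term in its main model

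*Protocol article*

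**What the plan says.** All references are to the protocol article.

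- **Study type.** The trial has 46 clusters: "Twenty-three clusters will be assigned to the treatment arm with In2Care® traps and 23 to the control arm without traps". Treatment and control sites are to be "matched according to retrospective incidence of reported dengue clinical cases over the previous 5 years and human population density".
- **Stratification scheme.** The same two factors appear again: "Clusters will be stratified according to historical dengue incidence and population density".
- **Recruitment.** Allocation is described as random: "Once clusters are identified and randomly assigned with appropriate stratification".
- **Outcomes.** "The secondary evaluation criterion is the entomological read out". For it, "20 GATs will be placed in each of 10 randomly selected treatment and 10 control sites matched with intervention sites for historical dengue incidence". Within each site, "Traps will be placed both inside and outside 10 randomly selected houses within each site". Weekly counts begin two weeks before the intervention.
- **Adult mosquito spatial distributions.** The main model takes "time (week), and intervention (Y/N) as fixed effects, and cluster ID and cluster risk designation as random effects", plus a term for routine public health mosquito control. A categorical building-density typology is described with a second series of analyses, based on distance to the nearest In2Care trap.
- **Objectives.** Reducing *Ae. aegypti* density is part of the primary objective, although Outcomes ranks the entomological read-out second.

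**The concern.** On the most natural reading, the two arms of the GAT subsample are chosen by different rules: treated clusters by a random draw, control clusters by matching. The matching clause names one factor where the trial as a whole uses two. Population density, which the sponsor thought worth matching on, is absent both from this clause and from the main GAT model.

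The comparison rests on 20 clusters. If human density is related to *Aedes* catch, a chance difference in density between the two groups of 10 would look like a trap effect or hide one. Random choice of houses acts within clusters, so it cannot balance density between them.

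**Working it through.** **1. Is there a plan figure to reproduce?** None exists for the GAT comparison. The only sample size in the protocol (2054 children per arm) concerns sero-conversion and does not bear on this point. By arithmetic, the subsample is 10 of 23 clusters per arm (43%), 20 clusters and 20 × 20 = 400 GATs.

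**2. The sections side by side.**

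| Section | Units | Factors named | Rule |
|---|---|---|---|
| Study type | 46 clusters | incidence, population density | matching |
| Stratification scheme | 46 clusters | incidence, population density | stratification |
| Outcomes (GAT) | 10 + 10 clusters | incidence | treated: random; control: matched |
| Main GAT model | 20 clusters | risk designation, cluster ID | random effects; no density term |

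The hot/intermediate/cold classification uses density as a covariate in the scan statistic. That adjusts how spots are identified; it does not balance density between arms.

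**3. How much balance is at stake?** This needs assumptions that the documents do not supply:

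- 46 cluster densities are drawn from a standard normal distribution, sorted and paired.
- Arm is random within pair.
- Three risk classes of 8, 8 and 7 pairs are independent of density.
- Ten treated clusters are drawn at random.

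The quantity is the difference in mean density between the 10 treated and 10 control GAT clusters, in units of the cluster SD. I re-ran the simulation (8,000 runs) and agreed with the figures below to within simulation error.

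| How the 10 controls are chosen | Mean difference | SD | Share beyond 0.5 SD |
|---|---|---|---|
| The treated clusters' own ideal partners | 0.00 | 0.06 | 0% |
| Random within risk class × density half | 0.00 | 0.19 | 1% |
| Random within risk class only | 0.00 | 0.33 | 12% |
| Plain random 10 of 23, no matching | 0.00 | 0.34 | 14–15% |

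Matching on incidence class alone therefore gives about 0.33 / 0.19 = 1.7 times the imbalance SD of the strata. It is practically the same as no matching. If risk class is correlated with density (0.5 assumed), the incidence-only SD falls to 0.29 and the share beyond 0.5 SD to 8.7%.

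**4. What this could do to the catch ratio.** Assume that log catch changes by b per SD of density. The 95% limit of the spurious rate ratio is exp(1.96 × b × SD). For b = 0.2 and SD 0.327: exp(1.96 × 0.2 × 0.327) = exp(0.128) = 1.14.

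| b (assumed) | Incidence class only (0.33) | Strata (0.19) | Ideal partners (0.06) |
|---|---|---|---|
| 0.1 | 1.07 | 1.04 | 1.01 |
| 0.2 | 1.14 | 1.08 | 1.02 |
| 0.3 | 1.21 | 1.12 | 1.04 |

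Each value, or its inverse, is a limit of chance variation around a ratio of 1, not an expected shift.

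**5. Discretionary choice, as a bound only.** If someone always took the densest eligible controls, the mean difference would be 0.77 SD. The spurious reduction in treated clusters would be 1 − exp(−0.77b), which is 7%, 14% or 21% for b = 0.1, 0.2 or 0.3.

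**The case against.** The strongest reply is that the Outcomes sentence is shorthand. Study type has already said that treatment and control sites are matched on both factors, so control sites matched with intervention sites may simply be those counterparts. The density match then carries over and nothing is lost. The word for random selection can also be read as covering both groups of 10. This stands as a possible reading, and it makes the loss conditional. It does not remove the need for a sentence. Stratification scheme assigns clusters only by general likeness and Recruitment speaks of stratification, so one-to-one partners are not documented and a unique counterpart may not exist.

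Second, re-matching without direction leaves a mean imbalance of zero. It does no worse than an ordinary random subsample, and the cluster random effect is there to carry between-cluster variation. This also stands: the cost is precision and chance imbalance.

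Third, the contrast with ideal partners (0.33 against 0.06, about fivefold) needs near-perfect pairing on density, which the protocol does not describe and for which it has density only at barangay level. The fair comparator is the strata, at about 1.7-fold.

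Fourth, there is mitigation: two pre-intervention weeks of catches make a baseline difference visible, and risk designation is in the model. This stands in part. The model lists neither a baseline-catch covariate nor an arm-by-time term, so if intervention is coded by arm those weeks do not by themselves correct a difference. The building-density typology is described with the distance analysis and is not human density.

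A reader might also infer that controls are picked by hand once arms are known, so that the result could be steered. The text does not say this. It names no selector, method or time, and subsampling after allocation is harmless when both arms follow the same random rule.

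**Conclusion.** The point holds in a limited form. The Outcomes section states a selection rule for GAT controls that names one factor, where the design sections name two, and it does not link those controls to the existing matched or stratified counterparts. The main GAT model does not make up for this.

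Unless the controls are the counterparts, chance imbalance in density is about 0.33 cluster-SD instead of about 0.19 with strata. These figures rest on assumed normal densities and three near-equal risk classes. Any translation into catch rests on an assumed slope of 0.1 to 0.3. The documents do not support reading this as a systematic bias. That would require discretionary selection, which the wording leaves open but does not describe; the 7–21% figures are a bound for that case.

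The outcome is ranked secondary, though it belongs to the primary objective. The change is worthwhile chiefly because it costs almost nothing before traps are deployed and cannot be made afterwards.

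**What to change.** - **Outcomes section.** State that the GAT clusters are drawn by computer before trap deployment, by the same random rule in both arms: either 10 whole matched sets, with GATs in both members, or equal numbers from each arm within each incidence-by-density stratum used for allocation. If the existing counterparts were always meant, say so and name both factors.
- **Main GAT model.** Account for the matched set or stratum, or add population density as a covariate.

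**Cost.** One sentence and one model term. GATs, clusters and visits are unchanged. A few degrees of freedom are lost among 20 clusters; a single density covariate uses fewer than a set term.
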